**Methods:**

The Hillrom study is a single-center, open-label, superiority,
cluster-randomized, parallel-group (1:1 allocation ratio) clinical trial
that will be conducted in a tertiary hospital. Two sets of three wards with
28 beds will be included (one as the intervention cluster and the other as
the control). The wards will be randomly assigned to use the Welch Allyn
Connex^®^ Spot Monitor/Hillrom Connecta™
automated solution (intervention cluster) or to maintain the usual routine
(control cluster) regarding rapid response team activation. The primary
outcome will be the absolute number of episodes of rapid response team
triggering in an appropriate time; as secondary outcomes, clinical features
(mortality, cardiac arrest, need for intensive care unit admission and
duration of hospitalization) will be assessed according to clusters in an
exploratory way. A sample size of 216 rapid response team activations was
estimated to identify a possible difference between the groups. The protocol
has been approved by the institutional Research Ethics Committee.

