#### Sample size calculation

A set of three wards with 28 beds will be considered the intervention cluster
(with the Welch Allyn Connex^®^ Spot Monitor (CSM)/Hillrom
Connecta™ solution), and a set of three wards with 28 beds will be
considered the control cluster. The average monthly number of episodes of
RRT triggering in the six selected wards is 12, of which it is estimated
that approximately 70% are triggered in a timely manner. For an absolute
increase of 18% in the proportion of timely RRT triggering (88%) in the
intervention group, with a test power of 90% and a significance level of 5%,
we estimated a sample size of 216 RRT activations.

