trial, the effectiveness of an automated vital signs monitoring system
associated with the automatic activation of the RRT on the absolute number
of triggers in an appropriate timely manner. Additionally, we will assess
clinical outcomes (mortality, cardiac arrest, need for ICU hospitalization
and duration of hospitalization) in an exploratory manner according to the
study groups. The assessment of RR manually is a limitation of this study,
considering that it is usually the least documented vital sign strongly
related to measurement errors;^(25)^ in this sense, the number of RRT activations might
be impaired. The unicentric characteristics and the small sample size are
other limitations of this protocol. Considering that we had no knowledge of
the intraclass correlation coefficient to make the appropriate formal
calculation for the cluster design, the sample size calculation was only a
preliminary estimate, characterizing this study as exploratory; on the other
hand, statistical analyses should adjust for the baseline values of RRTs in
the participating wards, which should reduce the random error of the
estimates. Additionally, the selection of the primary outcome was made
taking into account the exploratory design of this trial. We hope that from
the results obtained, it will be possible to carry out a multicenter study
with greater coverage so that we can confirm our findings. Another potential
limitation is performance bias, since it is an open-label study because of
the nature of the intervention. However, all other procedures involving the
management of patients in the wards will be maintained at the discretion of
the medical and nursing teams involved in the assistance. In addition, we
chose objective outcomes, and the team performing data collection and
statistical analysis will be blinded to the participant’s group, minimizing
the effects of this potential bias on the results.

The recruitment of the study was completed in September 2021. Currently, the
Hillrom study is in the data collection phase, identifying RRTs that have
been properly triggered. The study is expected to end in August 2022.

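### The 90% power quoted for 216 activations assumes independent observations and makes no allowance for clustering in six randomised wards

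*Protocol article*

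**What the plan says.** The protocol article's sample size section takes as its control rate "that approximately 70% are triggered in a timely manner. For an absolute" and sets the target as an "increase of 18% in the proportion of timely RRT triggering (88%) in the" group that receives the automated system. Power is set at 90% and significance at 5%. From these inputs it concludes: "we estimated a sample size of 216 RRT activations". It mentions neither an ICC nor a design effect.

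The abstract describes a "cluster-randomized, parallel-group (1:1 allocation ratio) clinical trial". The study setting and allocation sections assign wards to the groups, three per arm. The statistical analysis section plans generalised estimating equations with a uniform working correlation within ward, adjusted for the baseline number of timely activations.

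The discussion returns to the sample size. Because the ICC was not known for the appropriate "calculation for the cluster design, the sample size calculation was only a" preliminary estimate, and the study is called exploratory. It adds that baseline adjustment should reduce random error.

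**The concern.** The power statement and the design rest on different assumptions. Activations in one ward share staff, patient mix and distance from the rapid response team, so they may be correlated, and the planned model allows for this. The sample size section does not. Correlation within wards lowers the information in 216 activations, and with only six wards the loss can be large even when the ICC is small.

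Two things are at stake. A null result could be read as strong evidence against an 18-point improvement, on the strength of a 90% figure that the design has only if the ICC is practically zero. The discussion also hopes for a multicentre study to follow, and its planners need to know how sensitive this sample size is to clustering. Recruitment is by activation count alone, and above a modest ICC more activations in the same wards cannot make up the loss.

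**Working it through.** **Inputs from the sample size section:** p1 = 0.70, p2 = 0.88, difference 0.18, power 0.90, significance 0.05, total 216 (108 per arm at 1:1), three wards per arm. Sidedness is not stated. Two-sided is assumed because it reproduces the stated size; the one-sided version gives 172.

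**Step 1: reproduce 216.** Two independent proportions, pooled variance under the null, no continuity correction, mean proportion 0.79:

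n per arm = [1.960 × √(2 × 0.79 × 0.21) + 1.282 × √(0.70 × 0.30 + 0.88 × 0.12)]² / 0.18²

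= [1.960 × √0.3318 + 1.282 × √0.3156]² / 0.0324 = (1.129 + 0.720)² / 0.0324 = 105.5

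This rounds up to 106 per arm, 212 in total. At 108 per arm the power is 90.7%. The stated 216 is four activations above the formula, so it holds no usable design effect. Two-sided variants lie on either side: 206 unpooled or arcsine, 234 with continuity correction.

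**Step 2: add ward clustering.** Assumptions that the documents do not supply: the ICC values, equal wards of 216 / 6 = 36 activations, and no precision gain from baseline adjustment.

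- Design effect: DE = 1 + (36 − 1) × ICC.
- Effective size per arm: 108 / DE.
- Normal approximation: power = Φ[(0.18 × √(108/DE) − 1.960 × √0.3318) / √0.3156].
- Small-sample version: noncentral t with 6 − 2 = 4 df, critical value 2.776, noncentrality 0.18 / √(0.3156 × DE / 108).

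| ICC (assumed) | DE | Effective total | Power, normal | Power, t on 4 df |
|---|---|---|---|---|
| 0 | 1.00 | 216 | 90.7% | 70.5% |
| 0.001 | 1.035 | 209 | 89.7% | 69.1% |
| 0.01 | 1.35 | 160 | 80.4% | 58.2% |
| 0.02 | 1.70 | 127 | 70.7% | 49.3% |
| 0.05 | 2.75 | 79 | 49.9% | 33.8% |
| 0.10 | 4.50 | 48 | 33.0% | 22.8% |

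Example at ICC 0.01: 108 / 1.35 = 80 per arm; (0.18 × √80 − 1.129) / √0.3156 = 0.856; Φ(0.856) = 80.4%.

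**Step 3: can more activations restore 90%?** With three wards per arm and the normal approximation, n per arm = 106 × 3 × (1 − ICC) / (3 − 106 × ICC). At ICC 0.01 this is 314.8 / 1.94 = 162.3, so 163 per arm and 326 in total. At ICC 0.02 it is 311.6 / 0.88 = 354.1, so 355 per arm and 710 in total. The denominator reaches zero at ICC = 3 / 106 = 0.028. Above that, no number of activations in these six wards gives 90%.

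**The case against.** The strongest reply is that the authors have already disclosed the weakness. The discussion names the missing ICC, calls the size preliminary and the study exploratory, lists the small sample and single centre as limitations, and leaves confirmation to a later trial. That stands as mitigation: nothing is hidden, and a reader of the whole article is warned. It does not correct the sample size section, which states 90% without a caveat. Nor does it give a range or say that six wards are few for large-sample inference.

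The size of the loss also depends on choices made here. The ICC values are assumed. The t reference on 4 df is not in the article, and a small-sample correction may be specified in an analysis plan that is not shown. Baseline adjustment could recover some precision, though the article does not say how much, and a ward-level covariate would use a further degree of freedom. For these reasons the result is given as a range.

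A reader might infer three stronger points that the documents do not support:

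- **That the abstract also claims 90% power.** It does not. It gives 216 as the number needed to identify a possible difference. What it lacks is the caveat.
- **That there is one cluster per arm, so that no error rate can be stated.** The abstract's wording, "28 beds will be included (one as the intervention cluster and the other as" the control, invites this, and the sample size section uses the same terms. But the abstract also says that the wards are randomised, the setting and allocation sections agree, and the model takes the ward as the unit of correlation. Cluster there most plausibly means arm.
- **That superiority must be dropped from the design description.** It names the type of hypothesis and does not conflict with an exploratory aim.

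**Conclusion.** The point holds as a misstated power, not as an arithmetical slip: 216 follows from the stated inputs, but only for independent observations. For a trial that randomises six wards, 90% holds only if the ICC is essentially zero and a large-sample test is used. On the normal approximation, power falls just under 90% at ICC 0.001 and to a third at 0.10. If inference is referred to t on 4 df, it is about 70% even at ICC 0. All these figures assume equal wards and no gain from baseline adjustment. The discussion's disclosure reduces the harm but leaves the unqualified 90% in place.

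**What to change.** - In the sample size section, replace the 90% power statement with power, or detectable difference, over a stated ICC range (for example 0 to 0.10) for three wards per arm. Note that the number of clusters is small, and say what reference distribution and what gain from baseline adjustment are assumed.
- Carry the discussion's description of the size as preliminary and the study as exploratory into the sample size section and the abstract, where 216 appears without it.
- In the abstract and the sample size section, call each three-ward set an arm, so that the ward is plainly the randomised unit.

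Recruitment is reported as complete, so these are changes of statement only. They need no extra patients or wards. The cost is a less favourable stated power.

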#### Recruitment

The care team will be responsible for surveying all RRT triggering that
occurs in the randomized units. This survey is carried out using the
institution’s own printed form, as well as the collection of data recorded
on a platform provided by the company *Eritel
Telecomunicações Ltda*.

The information regarding triggering will be provided to IP-HCor for
registration and subsequent data collection from the medical records. In the
medical record, if any code generated by the platform is not identified, it
will be identified as a false triggering.

#### Allocation

The allocation of the selected wards to the intervention or control groups
will be performed randomly and stratified by blocks according to the size of
the cluster through the *sample* function of R 4.0.2 software
(R Core Team, Vienna, Austria, 2020). Only the IP-HCor statistician team
will have access to the allocation list.

#### Blinding

Considering the nature of the intervention, this will be an open-label study
in which the researchers, the care team and the patients will be aware of
the control or intervention clusters. During statistical analyses,
investigators and statisticians will be blinded to the study groups. To
avoid contamination between the groups as much as possible, the work
schedules of individual workers and the shifts of the nursing teams will
undergo the least possible change.

#### Data collection methods

In addition to the data regarding the recruitment period, information will be
collected to describe the characteristics of the clusters and patients
hospitalized in the selected wards for a period of three months prior to the
beginning of the protocol: January 2021, February 2021 and March 2021. The
institution’s Department of Epidemiology will provide the following
variables from institutional records (if available).

#### Cluster-level data

Baseline variables (at the time of hospitalization): age, sex, type
of hospitalization (surgical or clinical).Outcomes (during hospitalization): number of RRTs triggered, yellow
code rates, in-hospital mortality, duration of hospitalization, need
for ICU hospitalization, and number of cardiac arrests.

We will also present the total number of RRTs triggered in this period (at
the hospital level) and the number of hospital admissions on the selected
wards both in this period and during the study.

#### Individual-level data

Baseline variables (at the time of hospitalization): age, gender,
type of hospitalization, Charlson morbidity score.^(15)^Outcomes (during hospitalization): in-hospital mortality, duration of
hospitalization, need for ICU hospitalization, cardiac arrest, and
selected relevant clinical events (stroke, myocardial infarction,
and sepsis).

The nursing teams that work in the selected units will receive training prior
to the beginning of the clinical trial. During the training, the study
protocol and the Good Clinical Practices (GCP) guide will be presented.
Hands-on training in the handling of the device by a device specialist will
be provided to the care team at selected facilities that will use both Welch
Allyn Connex^®^ Spot Monitor (CSM) and Hillrom
Connecta™ devices.

Data will be collected through the physical records of patients who require
the triggering of the RRT code in the selected wards during the recruitment
period. These data will comprise age, sex, date of admission, reason for
hospital admission, diagnostic class of hospital admission, previous
comorbidities, date and time of yellow code triggering, physiological data
in the last 24 hours (HR, RR, SBP, diastolic blood pressure, temperature,
oxygen saturation, level of consciousness, capillary blood glucose [if
available], chest discomfort/pain, leukocytes [if available], presence of
sepsis, diuresis, poor general condition of the patient) collected at four
time points, problems related to yellow code triggering, clinical outcomes,
and hospital discharge/transfer/death. The frequency of vital signals
obtained will be the same between groups (four measurements 24/7 in each
group).

The analysis of the physical record and the input of data for the electronic
case report form (CRF) will be carried out by HCor professionals, who will
be previously trained in relation to the data capture system.

#### Data management

Data collection will be carried out through electronic CRF in the Academic
REDCap environment. Data are entered directly into the data capture system
by team members from the coordinating center, as there is still no
communication between the Welch Allyn Connex^®^ Spot Monitor
(CSM)/Hillrom Connecta™ solution and the REDCap system. All episodes
of RRT triggering will be confirmed by the care team, as false RRT
triggering may occur unduly or accidentally during the study period. The
sponsor will support and maintain the devices and software throughout the
period of use in the clinical trial. All nurse staff from the intervention
group will be trained to trigger a RRT manually in case the system fails; in
this case, this activation will be registered and dealt with as an intention
to treat.

Data monitoring will be carried out by a data management team to collect
*missing* data and inconsistencies using R software. Once
all data are entered into the system and all discrepant or missing data are
resolved, the statistician team will review and lock the database for
further statistical analysis.

#### Statistical analysis

The demographic and clinical characteristics of the sample will be summarized
according to the groups in absolute and relative frequencies for the
categorical variables; continuous variables will be presented by position
statistics (mean, median) and scale (standard deviation and interquartile
ranges).

The analysis for the primary outcome (events that trigger the RRT in a timely
manner) will be conducted with a logistic regression model considering
binomial distribution from generalized estimation equations, considering a
uniform work correlation matrix between patients of the same ward adjusted
for the baseline number of episodes of RRT triggering in an appropriate
timely manner. Other outcomes will be compared using a similar methodology
considering the response distribution that best fits the data. All results
will be presented considering measures of effect with respective 95%
confidence intervals.

Sensitivity analyses for the primary outcome considering time series
assessments and time of RRT activation (weekday *versus*
weekend; night *versus* day shifts) will be performed
comparing treatment groups. The results will be presented in graphs with
monthly indicators.

It is not expected that there will be a large amount of missing data.
However, if some of the primary and secondary outcomes are missing, the
missing data rate will be reported by group, and the values will be imputed
by chained equation multiple imputation methods using the mice package with
sample base characteristics.

All analyses will be performed with statistical R software 4.0.2 (R Core
Team, Vienna, Austria, 2020). Interim analyses or the participation of a
Data and Safety Monitoring Committee (DSMC) are not foreseen in the
protocol.

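### The primary GEE is clustered on only six wards with a ward-level covariate; under default GEE inference its nominal 95% intervals would cover only about 66% to 78%

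*Protocol article*

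**What the plan says.** All references are to the protocol article.

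- **Model.** Statistical analysis specifies a logistic model fitted by GEE. Its wording on clustering is "uniform work correlation matrix between patients of the same ward adjusted", and the covariate is each ward's count of timely activations before the trial. Effects are to carry 95% confidence intervals, and the other outcomes follow a similar approach.
- **Number of wards.** Sample size calculation refers to "RRT triggering in the six selected wards is 12, of which it is estimated" that about 70% are timely. It also says "A set of three wards with 28 beds will be considered the intervention cluster", with another three wards as control.
- **Unit.** The abstract calls the study a "cluster-randomized, parallel-group (1:1 allocation ratio) clinical trial". Allocation speaks of "The allocation of the selected wards to the intervention or control groups", so there the ward is the unit. The abstract and Sample size calculation instead call each set of three wards the cluster.
- **Defence of the covariate.** Discussion and trial status says the analysis should adjust for baseline RRT values in "the participating wards, which should reduce the random error of the" estimates.
- **Caveats.** The same section concedes a single centre, a small sample, an unknown ICC and an exploratory study. It does not mention that six clusters are too few for ordinary GEE inference.

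**The concern.** The sandwich variance is consistent as the number of clusters grows, not as the number of activations grows. Treatment and the baseline count both vary only between wards, so with the intercept three coefficients are estimated from six independent units. The sandwich estimate is then biased downwards, and a normal critical value ignores how poorly it is estimated. Both errors make the interval too narrow.

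A chance difference between three wards and three others would then often look like a device effect. The article calls this a superiority trial and hopes to build a multicentre study on the result, so the interval will be used for planning even if nobody treats it as confirmatory.

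**Working it through.** **1. The plan's own sample size.** Inputs from Sample size calculation: 70% v 88%, 90% power, 5% significance (sidedness not stated; two-sided taken). With the pooled normal formula, mean proportion 0.79:

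n per arm = [1.960·√(2·0.79·0.21) + 1.282·√(0.70·0.30 + 0.88·0.12)]² / 0.18² = 105.5, so 106 per arm and 212 in total.

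The stated 216 is within 2% of this; 108 per arm gives 90.7% power. So 216 treats activations as independent, with no design effect. It means 216/6 = 36 activations per ward.

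**2. Analytic size of the default test.** With k = 6 wards and p coefficients, the uncorrected sandwich variance is about (k − p)/k of what it should be. The size is therefore about 2·P(t on 6−p df > 1.96·√((6−p)/6)).

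- No covariate, p = 2: 1.96·√(4/6) = 1.600 on 4 df, size 18.5%, coverage 81.5%.
- Planned covariate, p = 3: 1.96·√(3/6) = 1.386 on 3 df, size 26.0%, coverage 74.0%.

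The ICC does not enter.

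**3. Simulation under the null.** Settings: six wards, 216 activations, 70% timely in both arms, beta-binomial wards, assumed ICC 0 to 0.10, about 4,000 trials per setting, exchangeable logistic GEE. Rejection rates at nominal 5%:

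| Model | Ward volumes | Sandwich, normal | Sandwich, t on 6−p df | Model-based SE, normal | Mancl-DeRouen, t on 6−p df |
|---|---|---|---|---|---|
| No covariate | equal | 18–19% | 8–9% | 18% | 2–3% |
| No covariate | unequal | 21–27% | 10–17% | 18–20% | 3% |
| Baseline count (planned) | equal | 26–29% | 11–14% | 23–25% | 2–3% |
| Baseline count (planned) | unequal | 30–34% | 15–19% | 20–26% | 2–3% |

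Null rates of 80% and 88% (ICC 0.02, equal wards) gave 28% for the planned model. A separate simulation of the planned model gave 22% to 28%. Together the range is 22% to 34%, hence coverage of 66% to 78%.

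**4. Does the covariate reduce random error?** It costs one of four residual df, so the 97.5% t quantile rises from 2.776 to 3.182. With chance imbalance added, an uninformative covariate widens a ward-level interval by about 25% (median) to 32% (mean). To break even, the baseline-outcome correlation r between wards must satisfy √(1 − r²) = 1/1.25 to 1/1.32, so r is about 0.60 to 0.65.

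Take the most favourable case: a perfectly stable ward effect and the baseline proportion as covariate. Then r = √(R_b·R_36), where R_n = n·ICC/(1 + (n−1)·ICC) and b is the number of baseline activations per ward.

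| b | ICC 0.01 | ICC 0.05 | ICC 0.10 |
|---|---|---|---|
| 6 | 0.12 | 0.40 | 0.57 |
| 18 | 0.20 | 0.56 | 0.73 |

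b = 6 follows from 12 a month over six wards for the three baseline months in Data collection methods (12·3/6). b = 18 follows if the 36 activations per ward arise within the six-month recruitment in Table 1 (6 per ward-month). The two rates do not agree, so both are shown. Only b = 18 with ICC 0.10 passes break-even. The planned covariate is a count, which also carries ward volume.

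**5. A valid comparison.** A t-test on six ward proportions (4 df, 36 activations each, 20,000 trials) has size 4.6% to 5.5%. Power for 70% v 88%:

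| ICC (assumed) | 0 | 0.01 | 0.02 | 0.05 | 0.10 |
|---|---|---|---|---|---|
| Power | 71% | 58% | 49% | 35% | 24% |

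**The case against.** **The faulted step is not written down.** The article names no variance estimator, no normal reference and no p-value for its primary test. A reader might infer that the plan commits to a large-sample Wald test. It does not say so; that is the default reading of a GEE with nothing else named, and an unseen analysis plan could add a correction. This stands, so the error rates are conditional on default inference. It does not remove the point: the article fixes the method, the clustering unit, the covariate and the number of wards, and that combination does not support the ordinary interval.

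**The study calls itself exploratory.** A reader might infer that a firm efficacy claim will rest on this model. Discussion and trial status does not support that; it looks to a later multicentre study for confirmation. This softens the consequence. But the stated caveats concern precision and power, and an interval covering about 74% is not a 95% interval under any label.

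**The unadjusted rates do not describe the plan.** Correct. The 18% to 20% for equal wards belongs to a model without the planned covariate and is given only for comparison.

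**The covariate could help.** It could, if ward differences are large and stable and the baseline data are ampler than 12 activations a month implies. The claim that it always harms is too strong; that it should reduce random error is unsupported in most of the range examined.

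**Perhaps only two clusters were randomised.** The wording about sets of three invites that reading, under which each arm has one cluster and no ward-level test is valid either. Allocation says wards were allocated. The text conflicts and does not establish the stronger reading.

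**Conclusion.** The point holds for the model as the article describes it. With default sandwich standard errors and a normal reference, the planned adjusted GEE has a false-positive rate of about 22% to 34% (analytic 26%) in place of 5%. Model-based standard errors do little better, at 20% to 26%. Outcomes analysed by the same approach share the defect.

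This rests on about 36 activations per ward on average, beta-binomial wards, six individually randomised wards and no small-sample correction elsewhere. The result is stable across assumed ICCs of 0 to 0.10 and null rates of 70% to 88%, and unequal ward volumes make it worse. The documents do not show that uncorrected inference will in fact be used, nor that any reported result will be wrong.

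**What to change.** 1. Make the primary analysis a comparison of one timely proportion per ward, with a two-sample t-test and confidence interval on 4 df. Alternatively, keep the GEE with a small-sample corrected variance and a t reference on 6 − p df. Both parts are needed, since the t reference alone leaves 8% to 19%. The two options are not equivalent: Mancl-DeRouen with t is conservative here, at about 2% to 3%.
2. Do not rely on a randomisation test. Three of six wards can be chosen in 20 ways, so the smallest two-sided p is 2/20 = 0.10, and stratified allocation leaves fewer.
3. Make the baseline-adjusted model supportive, and withdraw the statement in Discussion and trial status that adjustment should reduce random error.
4. Reconcile the abstract and Sample size calculation (set of three wards as the cluster) with Allocation (wards allocated). The 4-df test is valid only if the six wards were individually randomised.
5. Apply the same small-sample approach to the secondary outcomes.
6. State the power of the valid analysis from step 5 of the working beside the planned 90%.

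The cost is a paragraph of analysis text and standard R code, to be settled before database lock; the article describes data collection as still under way. The real price is wider intervals and power well below 90%. That shortfall comes from having six wards and a sample size without a design effect, and the corrected analysis only makes it visible.

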### Trial design

The Hillrom study (ClinicalTrials.gov Identifier: NCT04648579; 4th protocol
version [13/Apr/2021]) is a national, unicentric, cluster, parallel-group,
open-label, and superiority randomized clinical trial (allocation ratio
1:1).

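### The uniform working correlation in the primary GEE cannot be estimated reliably from six wards: it risks an inadmissible or failed primary fit and buys no precision

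*Protocol article*

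**What the plan says.** The Statistical analysis section of the protocol article commits the primary outcome to a binomial-logit GEE with a "uniform work correlation matrix between patients of the same ward adjusted" "for the baseline number of episodes of RRT triggering in an appropriate" time. The other outcomes are to be analysed in a similar way, with a response distribution chosen to suit each.

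The Sample size calculation section sets the number of clusters: "A set of three wards with 28 beds will be considered the intervention cluster", and a second set of three forms the control, so there are six wards. It targets 216 activations, 70% timely in control and 88% with the device. Under Allocation, the assignment "will be performed randomly and stratified by blocks according to the size of" the cluster. The Discussion says that the investigators did not know "the intraclass correlation coefficient to make the appropriate formal" calculation for a cluster design, and it calls the study exploratory.

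**The concern.** A uniform (exchangeable) structure needs one correlation, r, estimated from the data. Every activation in a ward with n activations then gets weight 1/(1 + (n−1)r). Two things make r hard to estimate here. Only six wards inform it, and three ward-level terms in the mean model absorb much of the variation between wards, which pulls r downward. If r falls below −1/(n_max−1), where n_max is the yield of the busiest ward, the working matrix is no longer positive definite. That ward then enters with a negative weight, or the iterations fail.

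What is at stake is whether the primary odds ratio can be computed and how the wards are weighted in it. If the fit fails, a replacement model has to be chosen once outcome data are in hand.

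**Working it through.** **Inputs.** From the document: six wards, 1:1; 70% v 88%; 216 activations, a mean of 216/6 = 36 per ward; 12 activations a month across the six wards (Sample size calculation) and recruitment April to September 2021 (Table 1), which gives 12 × 6 = 72, a mean of 12 per ward. Mean-model parameters: intercept, arm, baseline count = 3. Assumed, because not in the document: the ICC and the spread of ward yields.

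**The plan's own figure.** Two-sided 5%, 90% power, pooled test, no clustering:

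n per arm = [1.96·√(2·0.79·0.21) + 1.2816·√(0.70·0.30 + 0.88·0.12)]² / 0.18² = 105.5, so 106 per arm and 212 in total. This is close to the stated 216.

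**Where the matrix breaks.** The limit is −1/(n_max−1):
- n_max = 50 (illustrative): −1/49 = −0.020
- n = 36: −1/35 = −0.029
- n = 12: −1/11 = −0.091

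Take r = −0.025 as an illustration. A ward of 36 gets weight 1/(1 − 35·0.025) = 8.0. A ward of 50 gets 1/(1 − 49·0.025) = −4.4.

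**Why r is pulled down.** Let all wards have n activations. After three ward-level parameters are fitted, the six squared ward residual totals sum to roughly nσ²(1 + (n−1)·ICC) times a chi-square on 6 − 3 = 3 df. The moment estimate is negative when that sum is below 6nσ². So P(r < 0) ≈ P(χ²₃ < 6/(1 + (n−1)·ICC)).

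| n | ICC | 6/(1+(n−1)ICC) | P(r<0), approx. | Simulated, with no ward-rate variation |
|---|---|---|---|---|
| 36 | 0 | 6.00 | 89% | 88-90% |
| 36 | 0.02 | 3.53 | 68% | 69-70% |
| 36 | 0.05 | 2.18 | 46% | 48-49% |
| 12 | 0.05 | 3.87 | 72% | 72-76% |

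The hand calculation and the simulation agree, which confirms the three-degrees-of-freedom argument.

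**How often it matters.** The planned model (arm plus baseline count, 3 v 3 wards) was simulated about 2,000 times per setting, with a moment estimate of r. These are the 70% v 88% runs; SD is that of the log odds ratio. A rate CV of 0 means that yields differ only by chance.

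| Activations | Rate CV | ICC | r<0 | Inadmissible | Not converged | SD, uniform / independence |
|---|---|---|---|---|---|---|
| 216 | 0 | 0.02 | 70% | 8.7% | 4.9% | 0.618 / 0.611 |
| 216 | 0 | 0.05 | 48% | 4.9% | 2.9% | 0.828 / 0.831 |
| 216 | 0.4 | 0.02 | 74% | 22.0% | 7.7% | 0.637 / 0.633 |
| 216 | 0.4 | 0.05 | 54% | 12.8% | 4.6% | 0.873 / 0.870 |
| 72 | 0 | 0.02 | 83% | 17.1% | 7.7% | 0.977 / 0.969 |
| 72 | 0 | 0.05 | 76% | 11.6% | 4.8% | 1.097 / 1.099 |
| 72 | 0.4 | 0.02 | 83% | 27.8% | 8.7% | 0.975 / 0.963 |
| 72 | 0.4 | 0.05 | 78% | 20.0% | 5.7% | 1.153 / 1.145 |

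Further simulations over ICC 0.01 to 0.05 gave inadmissibility of about 3-22% and non-convergence of about 4-13% at 216, and about 8-28% and 7-13% at 72. Non-convergence depends on the code and its iteration rule. Non-converged fits are left out of the SD comparison.

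**Effect on the odds ratio.** Every model term is at ward level, so the estimating equation is Σ xᵢwᵢΣ(yᵢⱼ − μᵢ) = 0 with wᵢ = 1/(1 + (nᵢ−1)r). With equal nᵢ, the common weight cancels and the uniform and independence fits coincide. With unequal yields, the odds ratio differs by more than 25% from the independence fit in at most about 8% of trials at 216 and in about 13-22% at 72.

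**Inference.** With an uncorrected sandwich Wald test at z = 1.96 and no true effect, 216 activations, the rejection rate is 25-31% with the uniform structure and 26-32% with independence.

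**The case against.** The strongest defence is that an exchangeable GEE is a standard choice for a cluster trial, that its consistency does not depend on the working correlation being right, and that the article calls the study exploratory with an unknown ICC. All of this is true, but consistency is an argument about many clusters. With six, an inadmissible matrix or a failed fit remains a practical possibility.

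Several points limit the concern, and they stand:

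- A reader might infer from the high rates of negative r that most fits would be faulty. They would not. Between −1/(n_max−1) and zero, all weights are positive and the estimator is valid.
- Nothing happens if ward yields are exactly equal, and the wards are selected for a similar patient profile. Activations are random counts, though, and chance variation alone produced inadmissible fits. Stratifying on cluster size suggests unequal sizes but does not prove them.
- At 216 activations, large shifts in the odds ratio are uncommon. The 72-activation case rests on the stated monthly rate and calendar, while the Timeline section says recording continues until the calculated number is reached.
- A reader might infer that a replacement model could be picked to favour an arm. The Blinding section keeps investigators and statisticians blind to group during analysis, which softens this. A fallback rule may also stand in an analysis plan that is not shown, so its absence from the article is not part of the point.

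**Conclusion.** The point holds as a cheap improvement. The protocol states a working structure that six wards with three ward-level parameters cannot support. Under the assumed ICC of 0.01 to 0.05 and ward-rate CV of 0 to 0.4, the primary fit has a modest but real chance of being inadmissible or failing, and there is no gain in precision to set against that risk. The size depends on ward yields and an ICC that the document does not give.

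Two stronger readings are not supported. One is that an independence structure would return the simple contrast of "that approximately 70% are triggered in a timely manner. For an absolute" "increase of 18% in the proportion of timely RRT triggering (88%) in the" device group. It would not, because the adjustment for baseline timely episodes remains, so either fit is an adjusted odds ratio. The other is that changing the working correlation makes six-ward inference sound. It does not: the uncorrected sandwich is badly anti-conservative under both structures.

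**What to change.** In the Statistical analysis section, replace the uniform working correlation by independence and keep the ward as the cluster for the robust variance. State a small-sample corrected variance with a t reference (6 − 3 = 3 degrees of freedom is the natural count). The second part is needed in its own right, because the first does not repair the inference. Show the uniform fit only as a sensitivity analysis, and only when it converges with r > −1/(n_max−1). Apply the same rule to the other outcomes analysed in the same way. Make the change before the database is locked; the article describes the trial as still in data collection.

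The cost is a short change of text and two software settings, with no new data. The statistical downside is small: at ICC 0.2 and ward-volume CV 0.6, the SD of the log odds ratio is 1.68 under independence against 1.64 under the uniform structure (1.68/1.64 = 1.02, about 2% larger).
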